## Abstract

**Background:**

Palliative care staff commonly experience workplace stress and distress. General stressors include unmanageable workloads and staff shortages. Stressors specific to palliative care include regular exposure to death, loss and grief. The COVID-19 pandemic exacerbated exhaustion and burnout across the healthcare system, including for those providing palliative care. Evidence based psychological support interventions, tailored to the needs and context of palliative care staff, are needed. Acceptance and Commitment Therapy (ACT) is an established form of cognitive behavioural therapy which uses behavioural psychology, values, acceptance, and mindfulness techniques to improve mental health and wellbeing. ACT is effective in improving workplace wellbeing in many occupational settings. Our study examines the acceptability and feasibility of an online ACT-based intervention to improve mental health and wellbeing in staff caring for people with an advanced progressive illness.

**Methods:**

We plan a single-arm feasibility trial. We will seek to recruit 30 participants to take part in an 8- week online ACT-based intervention, consisting of three synchronous facilitated group sessions and five asynchronous self-directed learning modules. We will use convergent mixed methods to evaluate the feasibility of the intervention. Quantitative feasibility outcomes will include participant recruitment and retention rates, alongside completion rates of measures assessing stress, quality of life, wellbeing, and psychological flexibility. Focus groups and interviews will explore participant perspectives on the intervention. We will run a stakeholder workshop to further refine the intervention and identify outcomes for use in a future evaluation.

**Results:**

We will describe participant perspectives on intervention acceptability, format, content, and perceived impact, alongside rates of intervention recruitment, retention, and outcome measure completion.

**Conclusion:**

We will show whether a brief, online ACT intervention is acceptable to, and feasible for palliative care staff. Findings will be used to further refine the intervention and provide essential information on outcome assessment prior to a full-scale evaluation.

## Introduction

Healthcare professionals working in palliative care settings commonly experience stress and distress
^
1–
3
^. General stresses include unmanageable workload and staff shortages. Specific stressors occur as a result of caring for patients with complex physical conditions, and regular exposure to death, loss, and grief. In 2020-21, the COVID-19 pandemic led to increased stress and distress within the health and social care workforce
^
4–
8
^, including palliative care
^
9,
10
^. As a result of the pandemic, healthcare staff encountered rapidly changing clinical roles, new modes of service delivery and increased patient volumes, coupled with risk of infection. A considerable proportion experienced mood and sleep disturbances, raising concerns about risks to mental health
^
8
^. 

Despite the occurrence of workplace stress and distress, evidence based psychological support for palliative care staff is lacking. A 2019 Nursing Standard-Marie Curie survey involving 5,346 UK nurses and healthcare assistants involved in end-of-life care, found that one-third reported insufficient support at work to manage grief and emotional stress from caring for dying patients
^
11
^. In 2020, the same survey with 894 respondents, revealed this proportion had increased to 45%, with visiting restrictions due to the pandemic placing additional emotional burden on staff who needed to balance the safety of patients with their needs to be together with their families
^
12
^. A systematic review prior to the pandemic identified only nine papers evaluating psychosocial interventions for palliative care staff and concluded that there was an urgent need to address the lack of intervention development work and high-quality research in this area
^
13
^. Flexible, accessible, scalable and cost-effective psychological support interventions are now more important than ever. 

We propose an Acceptance and Commitment Therapy (ACT) based psychological intervention to improve wellbeing, stress, and distress in palliative care staff. ACT is an established form of cognitive behavioural therapy which uses behavioural psychology, values, acceptance and mindfulness techniques to improve mental health and wellbeing
^
14
^.

ACT principles target the kinds of responses that clinicians identify as helpful: being present, finding purpose, acceptance, perspective taking and engaging in life
^
15
^. Recent systematic reviews and meta-analyses show that ACT is efficacious in treating stress, anxiety and depression in a range of settings
^
16–
18
^, including when delivered online
^
19,
20
^. Drawing on evidence of effectiveness in other occupational and healthcare settings
^
16,
17,
21–
23
^, we propose that an ACT-based psychological intervention has strong potential to improve mental health and wellbeing in palliative care staff.

We aim to develop, and test the feasibility of an online ACT-based intervention to enhance workplace wellbeing of staff working with terminally ill and dying patients, and their families. Our research will answer the following questions:

Is an online ACT intervention feasible and acceptable to palliative care staff?What is the experience of palliative care staff undertaking ACT training?What are the barriers and facilitators to implementing an online ACT intervention for palliative care staff?Is there preliminary evidence that ACT training leads to improvements in workplace wellbeing and stress in palliative care staff?What are the implications for future evaluation research, including sample size and outcome measures?

## Methods

### Design

A single-arm feasibility trial of a brief ACT-based intervention for staff providing palliative care for terminally ill adults. We will use convergent mixed methods
^
24
^ to evaluate the feasibility of the proposed intervention. 

### Setting

The study will be hosted by Marie Curie Scotland. Marie Curie is the largest independent provider of end-of-life care and the largest charitable provider of hospice-based care in Scotland. Two Marie Curie hospices, located in Edinburgh and Glasgow, provide short-term inpatient hospice care, outpatient services (including day services), home visits and family support, to terminally ill people and families in their surrounding areas. Across Scotland, the Marie Curie Nursing Service (MCNS) provides care in the last days of life to people in their own homes.

### Participants and sample size

Participants will be recruited from two Marie Curie hospices and from the Marie Curie Nursing Service (Scotland). We will seek a sample size of approximately 30 participants. As this is a feasibility study, sample size has not been formally calculated. Our target sample size is based on prior experience, resources available and the format of the intervention. 

**
*Inclusion criteria.*
** The intervention will be offered to health and social care professionals providing direct support to patients and families, including nursing and medical staff, allied health professionals, social workers, and healthcare assistants. 

**
*Exclusion criteria.*
** Staff who have previously undertaken Acceptance and Commitment Therapy training will be excluded.

### Participant recruitment

Members of the research team will discuss the proposed study with service managers and clinical leads across Marie Curie Scotland. The study will be promoted via hospice newsletters, posters, internal email lists and via relevant Marie Curie internal online forums. The research team will run an online information session for potentially interested participants via MS Teams. 

Interested staff members will be directed to seek approval from their line manager in the first instance, if they are interested in taking part. Potentially interested participants will be emailed the participant information sheet, and a link to an online consent form. Following consent, they will be invited to complete an online participant characteristics form (gender; age band; ethnicity; role and number of years’ experience in palliative care) which will be used to describe the sample, and stored separately from any outcome data.

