### Intervention design and content

**
*Location.*
** The online Acceptance and Commitment Therapy (ACT) intervention will be hosted using MS Teams. Participants will be able to join from their usual workplace or home setting. Support will be provided from the research team and the admin team at each hospice for participants who need to access a hospice PC in a quiet location for the purpose of this study.

**
*Facilitation.*
** The intervention will be delivered by a Peer Reviewed ACT Trainer and Fellow of the Association for Contextual Behavioural Science (DG) and facilitated by a research psychologist (AF). DG will lead the virtual classroom sessions. AF will co-ordinate module delivery, manage the online platform and liaise and respond to technical support queries.

**
*Online platform.*
** MS Teams will be used as the training platform, as this supports a range of media, enables chat, and is used widely within health and social care organisations. An MS Team will be set up for intervention delivery, and participants will be invited to join once they consent to the taking part. All participants will be invited to access the online platform in advance of the first session, and individual support, as well as printed resources, will be provided to support access. All intervention materials made available via MS Teams. 

**
*Content.*
** The intervention will cover key ACT processes including being present, finding purpose, perspective taking and engaging in life values (
Table 1). The content has been informed by previous interventions delivered by the team for health professionals in other settings, as well as research on occupational stress, wellbeing, self-compassion and resilience in palliative care
^
3,
15,
25–
28
^. The content is described in a draft manual, which will be revised and shared on the ISRCTN registry on completion of the study.

**Table 1. T1:** Overview of intervention content.

Week	Module	Time required	Content	Delivery mode
*1*	** *Introduction to ACT* **	**90 minutes**	**Introduction**	Synchronous online virtual classroom Led by an ACT trainer (DG)
*2*	** *Values* **	30 minutes	Identifying and acting in line with your values	Self-directed, asynchronous materials Group chat Homework
*3*	**Awareness**	30 minutes	Present moment awareness; mindfulness; grounding	Self-directed, asynchronous materials Group chat Homework

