### Data management

**
*Personal data.*
** Personal data (participant name, email address, age band, gender, role, years working in palliative care) will be stored in a secure file in the University of Edinburgh DataStore. This is password protected and encrypted storage. Participants will be allocated a Participant ID for the study. The Participant ID will be used when completing the online questionnaire. Outcome data will be kept separate from personal data throughout the study. The code break file will be held in a separate password protected folder within the DataStore only accessible by the Co-Principal Investigators (AF and DG). 

**
*Transfer of data.*
** Focus group and interview data collected at the host organisation (Marie Curie) will be stored in a secure location on MS Teams, accessible only to participants and the research team (and deleted once transcription has taken place). Data will be anonymised and transcribed by a member of the research team, and then transferred via secure email to the University of Edinburgh DataStore. 

**
*Data storage.*
** All date files will be stored in a secure location – the University of Edinburgh DataStore. Personal data will be held for no longer than 2 years after completion of the study. The Co-Principal Investigators will be responsible for deletion of data. Anonymised data will be retained indefinitely to inform future research.

**
*Confidentiality.*
** Participants will be allocated a Participant ID following recruitment. The Participant ID will be used when completing online questionnaires throughout the study. The Participant ID will be linked in one stand-alone file held in the DataStore, and only accessed if the participant has forgotten their ID and needs to be reminded. We do not plan any analysis that would potentially identify a participant, however, if there is any chance of this occurring, we will collapse the small group data in the final anonymised file, so there is no chance of identification (e.g. If only one male participated, outcome data by gender would be amalgamated.) Participants will be known to each other but will be reminded throughout the study that all discussions should remain confidential.

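### Two service types are recruited, but no employing service appears among the participant fields described and every feasibility target is pooled, so poor uptake or completion in the Nursing Service could go unseen

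*Protocol article*

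**What the plan says.** Under Participants and sample size, the protocol article states: "Participants will be recruited from two Marie Curie hospices and from the Marie Curie Nursing Service (Scotland"). The Setting section separates the two service types. The hospices in Edinburgh and Glasgow "provide short-term inpatient hospice care, outpatient services (including day services), home visits and family support", whereas across Scotland "the Marie Curie Nursing Service (MCNS) provides care in the last days of life to people in their own homes".

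Participant recruitment says that consenting staff will be "invited to complete an online participant characteristics form (gender; age band; ethnicity; role and number of" years in palliative care, "which will be used to describe the sample, and stored separately from any outcome data". Data management gives a second list: "Personal data (participant name, email address, age band, gender, role, years working in palliative care"). Neither list mentions service or site.

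The feasibility outcomes under Data collection, analysis and management carry four targets, all for the whole sample: 24 to 30 recruits; two-thirds completing the intervention; at least two-thirds of starters completing the outcome measures; and 50–75% of recruits taking part in a focus group or interview. No breakdown by service is described.

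Under Location, the research team gives access support together with "the admin team at each hospice for participants who need to access a hospice PC in a quiet location". The same section also lets everyone join from home or work and offers individual support and printed resources.

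**The concern.** The research questions ask whether the online course is feasible for palliative care staff and what helps or hinders its implementation. The study chose to recruit from two service types whose staff may not find it equally easy to take part: the only on-site help described is at the hospices. A pooled rate cannot show whether both types were recruited and retained. The characteristics form is meant to describe the sample, yet as described it leaves out which service each participant came from.

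At stake is how far the feasibility conclusion reaches. If one service type contributes few participants or loses most of them, a statement about palliative care staff as a whole would rest on the other type, and a later evaluation could be planned without knowing this.

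**Working it through.** The article gives no sample size calculation, so there is no figure to reproduce. The check asks whether, and when, a pooled target can hide a poor result in one service type.

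**Inputs from the article.** N between 24 and 30; target of two-thirds. For intervention completion the printed denominator is those who completed, which is circular. I assume starters, as for the outcome measures, and that everyone recruited starts.

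**Assumptions.** The number of Nursing Service staff (m) and the completion rate in each service type are not in the article, so a range is shown.

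**Step 1: completers needed.** 2/3 × 30 = 20; 2/3 × 24 = 16.

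**Step 2: can the target be met with no Nursing Service completers?** Hospice completion would have to be (completers needed)/(N − m).
- N = 30: m = 4 gives 20/26 = 77%; m = 6 gives 20/24 = 83%; m = 10 gives 20/20 = 100%. Above 10 it is impossible.
- N = 24: m = 6 gives 16/18 = 89%; m = 8 gives 16/16 = 100%. Above 8 it is impossible.

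The target can therefore be met with zero Nursing Service completers as long as they are no more than one-third of the sample.

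**Step 3: same pooled figure, different pictures.** With 20 hospice and 10 Nursing Service staff, 18/20 (90%) and 2/10 (20%) give 20/30 = 67%. So do 13/20 (65%) and 7/10 (70%).

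**Step 4: how likely is masking?** Let X ~ Bin(30 − m, p_H) be hospice completers and Y ~ Bin(m, p_N) Nursing Service completers, independent. The exact probability P(X + Y ≥ 20) is:

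| Nursing Service staff (m) of 30 | p_H = 90%, p_N = 20% | p_H = 80%, p_N = 20% |
|---|---|---|
| 4 | 0.994 | 0.833 |
| 6 | 0.965 | 0.669 |
| 8 | 0.857 | 0.454 |
| 10 | 0.614 | 0.247 |
| 12 | 0.313 | 0.106 |
| 15 | 0.060 | 0.019 |

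**Step 5: the other targets.** The recruitment target can be met by 24 hospice staff and nobody from the Nursing Service. The lower end of the focus group or interview target, 50% × 30 = 15, can be met by hospice staff alone (15 of 20 in the split above).

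**Step 6: what a breakdown could show.** Clopper–Pearson 95% intervals: 0/10, 0–31%; 2/10, 3–56%; 7/10, 35–93%; pooled 20/30, 47–83%. Counts by service type would be imprecise, so they support description and not a test.

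**The case against.** The strongest reply is that this is an omission in a condensed article and not an error. Several parts of that reply stand.

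- **The lists may not be complete.** The form includes ethnicity and the personal-data list does not, so the bracketed fields cannot be read as exhaustive. A reader might infer that service is never recorded; the article shows only that it is not among the fields described.
- **Service may be recoverable.** Staff need line-manager approval, and the team holds names and email addresses. Recruitment, attendance and focus group participation are counts of identifiable people. However, no such use is described, and the file linking participant IDs is to be opened only for forgotten IDs, which matters for questionnaire completion by service.
- **Barriers are studied in other ways.** Focus groups are open to all, those who drop out are invited to interview or asked for reasons, and the workshop reviews feasibility data with managers. These can reveal setting-specific barriers but give no rate by service.
- **The contrast between services is limited.** There are two service types, not three unlike services, and the hospices also make home visits. Home working does not mark out the Nursing Service, and Nursing Service staff are not said to be barred from hospice PCs.

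A reader might also infer that meeting the targets would lead the study to declare feasibility for both service types and take both into the full evaluation. The article does not say so: the targets are nowhere made a progression rule.

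What remains is that role cannot stand in for service, since nurses and healthcare assistants may come from either type. An analysis plan can break results down by service only if service is available for each participant.

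**Conclusion.** The point holds as a low-cost improvement, not as an error in the plan. As described, participant data include no employing service and all four targets are pooled. The targets can therefore be met with poor Nursing Service uptake or completion, and in the extreme with no Nursing Service completers when they are up to one-third of the sample.

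How likely this is depends on a split and on completion rates that the article does not give. Under the assumed rates, masking is likely when the Nursing Service makes up about a quarter of the sample or less and hospice completion is high. It is unlikely at an even split (0.06 or 0.02). Nothing here shows that Nursing Service staff will do worse, or that the sample size should change.

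**What to change.** 1. Record employing service (hospice or Nursing Service) for each participant. The Study status section says data collection is under way, so it is too late to rely on the enrolment form. Take service from recruitment records or obtain it through a short amendment. Let the amendment also cover attaching the service code to the participant ID, so that questionnaire completion can be counted by service.
2. Report the four feasibility counts (recruited, completed the intervention, completed the measures, took part in a focus group or interview) by service type as well as overall. Keep this descriptive, with no separate targets and no tests.
3. State that the feasibility conclusion covers only the service types actually recruited and retained.
4. Correct the circular denominator of the intervention completion target, so that the breakdown has a defined base.

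The cost is one variable, a two-column table and a brief amendment. The downside is small, imprecise cells and slightly higher identifiability. Combining the two hospices, and applying the rule on collapsing small groups already given under Confidentiality, limits the second.

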### Intervention design and content

**
*Location.*
** The online Acceptance and Commitment Therapy (ACT) intervention will be hosted using MS Teams. Participants will be able to join from their usual workplace or home setting. Support will be provided from the research team and the admin team at each hospice for participants who need to access a hospice PC in a quiet location for the purpose of this study.

**
*Facilitation.*
** The intervention will be delivered by a Peer Reviewed ACT Trainer and Fellow of the Association for Contextual Behavioural Science (DG) and facilitated by a research psychologist (AF). DG will lead the virtual classroom sessions. AF will co-ordinate module delivery, manage the online platform and liaise and respond to technical support queries.

**
*Online platform.*
** MS Teams will be used as the training platform, as this supports a range of media, enables chat, and is used widely within health and social care organisations. An MS Team will be set up for intervention delivery, and participants will be invited to join once they consent to the taking part. All participants will be invited to access the online platform in advance of the first session, and individual support, as well as printed resources, will be provided to support access. All intervention materials made available via MS Teams. 

**
*Content.*
** The intervention will cover key ACT processes including being present, finding purpose, perspective taking and engaging in life values (
Table 1). The content has been informed by previous interventions delivered by the team for health professionals in other settings, as well as research on occupational stress, wellbeing, self-compassion and resilience in palliative care
^
3,
15,
25–
28
^. The content is described in a draft manual, which will be revised and shared on the ISRCTN registry on completion of the study.

**Table 1. T1:** Overview of intervention content.

Week	Module	Time required	Content	Delivery mode
*1*	** *Introduction to ACT* **	**90 minutes**	**Introduction**	Synchronous online virtual classroom Led by an ACT trainer (DG)
*2*	** *Values* **	30 minutes	Identifying and acting in line with your values	Self-directed, asynchronous materials Group chat Homework
*3*	**Awareness**	30 minutes	Present moment awareness; mindfulness; grounding	Self-directed, asynchronous materials Group chat Homework
*4*	** *Review of materials* **	**90 minutes**	Review, troubleshooting, clarifying materials. Discussion.	Synchronous online virtual classroom Led by an ACT trainer (DG)
*5*	** *Openness* **	30 minutes	Developing self-awareness, becoming more open, making room.	Self-directed, asynchronous materials Group chat Homework
*6*	** *Defusion* **	30 minutes	Unhooking from difficult thoughts and feelings	Self-directed, asynchronous materials Group chat Homework
**7**	**Compassion**	30 minutes	Kindness to self and others	Self-directed, asynchronous materials Group chat Homework
**8**	**Review and** **trouble shooting**	**90 minutes**	Review, troubleshooting, clarifying materials. Discussion.	Synchronous online virtual classroom Led by an ACT trainer (DG)

**
*Format.*
** There will be 8 modules delivered via MS Teams over an 8-week period (
Table 1). Delivery will be via three synchronous virtual classroom sessions and five asynchronous, self-directed, e-learning modules. The three virtual classroom modules will be interactive expert-led sessions. The five self-directed e-learning modules will consist of online reading materials, pre-recorded videos, and reflective exercises. Participants will be encouraged to share experiences with each other and ask questions or seek clarification via the online chat function within MS Teams. Participants will be provided with a workbook (hard-copy) outlining the content for each week alongside related exercises. The workbook can be accessed here:
https://doi.org/10.1186/ISRCTN14313559

**
*Homework.*
** Participants will be asked to complete ‘homework’ each week to reflect on the material and how it relates to themselves and their work. Homework will be brief and non-obligatory but encouraged. Examples of homework would include practicing brief mindfulness exercises or exercises to enhance compassionate responses. Homework will be described in the workbook. 

**
*Adherence*
** To facilitate adherence, participants will also be sent a weekly reminder to alert them when new content is made available. To facilitate engagement, participants will be encouraged to share their experiences of the intervention, and any questions they might have via the online chat function (within MS Teams). 

**
*Benefits of participation.*
** Participants will receive introductory training in ACT targeted at using this for their own stress management benefit and will be given the opportunity to engage with a range of strategies to improve their workplace and personal well-being over time. 

**
*Distress protocol.*
** It is unlikely that a participant will experience negative consequences as a result of participating in the proposed intervention. However, if a participant does report feeling heightened stress or distress, the course leader, a Clinical Psychologist, will discuss immediate concerns with them, and will signpost them to additional resources and support as appropriate. This may include: i) the Marie Curie Employee Assistance Programme (EAP) which includes practical information and emotional support guidance as well as access to trained counsellors, ii) to their line manager or HR manager if appropriate, iii) to a Marie Curie hospice-based Clinical Psychologist. Any unintended harms will be recorded by the Co-Principal Investigators and described as part of the research findings.

**
*Ancillary and post-trial care.*
** Should any participant express a need for additional or continued psychological support on completion of the intervention, they will be directed to additional support, in line with the distress protocol.

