### Data collection, analysis and management

**
*Quantitative data collection.*
** Five key outcomes will be assessed prospectively, via JISC online survey (
www.onlinesurveys.ac.uk) at four time-points – before commencement of the intervention, mid-way through the intervention, on completion of the intervention and one-month post-completion. (
Table 2). This will allow examination of preliminary evidence for changes in outcomes collected by questionnaire over the course of the intervention, as well as questionnaire completion rates to inform the design of a future evaluation. As we are most interested in changes in outcomes that are sustained beyond intervention delivery, our main exploratory analysis will focus on the change in outcomes pre-intervention versus 4 weeks post intervention. This data will help us identify key outcomes and sample size needed for a future evaluation

**Table 2. T2:** Schedule of enrolment, interventions, and assessments.

WEEK	Pre-intervention	Wk1	Wk2	Wk3	Wk4	Wk5	Wk6	Wk7	Wk8	Wk9	Wk10	Wk11	Wk12	Wk13-16
**EVALUATION** **TIMEPOINTS**	**t0**			**t1**				**t2**					**t3**	

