### Monitoring

**
*Role of sponsor and funder.*
** The Co-Principal Investigators (AF and DG) are employees of the sponsor organisation (University of Edinburgh) and have honorary contracts at the host site (Marie Curie). They will have a direct role in study design; collection, management, analysis, interpretation of data; writing of the report; and the decision to submit the report for publication. The study is funded by Marie Curie:
www.mariecurie.org.uk.

**
*Data controller, breaches and monitoring.*
** The University of Edinburgh is the data controller for this study. Any data breaches will be reported to the University of Edinburgh Data Protection Officers who will onward report to Marie Curie, according to the appropriate timelines, if required. As this is a low-risk single-arm feasibility study, a data monitoring committee is not required.

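### The only stated route into the harms record is a participant's own report, and the two investigators who run the course keep that record, so few or no recorded harms could not be read as reassurance

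*Protocol article*

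**What the plan says.** The Distress protocol paragraph (Intervention design and content) opens with an expectation: "It is unlikely that a participant will experience negative consequences as a result of participating in the proposed intervention". It then gives one trigger and one response: "if a participant does report feeling heightened stress or distress, the course leader, a Clinical Psychologist, will discuss immediate concerns with them". It closes with the reporting promise: "Any unintended harms will be recorded by the Co-Principal Investigators and described as part of the research findings".

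Two other places show who keeps the record. The Facilitation paragraph describes the trainer as a "Fellow of the Association for Contextual Behavioural Science (DG) and facilitated by a research psychologist (AF". The Monitoring section states: "The Co-Principal Investigators (AF and DG) are employees of the sponsor organisation". The initials match, so the recorders are the person who delivers the course and the person who facilitates it. Monitoring adds: "As this is a low-risk single-arm feasibility study, a data monitoring committee is not required".

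On what participants are asked, the Data collection section says: "Five key outcomes will be assessed prospectively, via JISC online survey". The surveys are given before, mid-way through, at the end of and one month after the course. Participants who drop out are invited to a brief interview, or asked for permission to note their main reason. Everyone is invited to a focus group one month after the course. A qualitative researcher who is not a Co-Principal Investigator collects these qualitative data. Table 2 lists the data items by week and has no row for harms.

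**The concern.** The article commits to describing harms as a finding, but the one mechanism it sets out waits for the participant to speak first. Several features of the setting could discourage that. Staff need line-manager approval to join, they take the course with people they know, and the places to which a distressed participant may be directed include the line manager or HR manager. Those who would hear of a harm and record it are running the course, and the same paragraph already calls negative consequences unlikely.

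What is at stake is how the harms statement can be read. The study is presented as the first step towards a large-scale evaluation in a workforce described as stressed. If few or no harms are reported, a reader cannot tell whether few occurred or few reached the record.

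**Working it through.** There is no figure in the plan to reproduce. The article gives no harm rate and says that the sample size was not formally calculated. The check has two parts.

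**1. Does any source in which participants are actually asked something feed the harms record?**

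| Source | What the article says is asked | Stated link to harms record |
|---|---|---|
| Surveys at t0 to t3 | Five scales: 10 + 30 + 14 + 13 + 23 = 90 items on stress, professional quality of life, wellbeing, mindful healthcare and psychological flexibility | None. Reported by mean, SD, range and similar; the main interest is improvement from T0 to T3 |
| Drop-out interview or noted reason | Reasons for leaving | None |
| Focus groups | Experience, most and least useful elements, perceived changes, possible effect on care; harm is not a named topic | None |
| Participant's own report | Nothing is asked; the participant starts it | Same paragraph as the harms record |

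Two further limits apply.
- Focus groups and interviews together have a participation target of 50 to 75% of those recruited. With 30 recruited, that is 0.50 × 30 = 15 to 0.75 × 30 = 22.5 people.
- With pairwise deletion, anyone without a T3 score drops out of the T0 to T3 change, so the scores say little about people who leave.

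**2. What could incomplete capture do to the report?** (illustration only)

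Inputs: n = 30 or 24, the upper and lower ends of the recruitment target. Assumed, and not in the document: p, the true risk that a participant is harmed, and s, the share of harms that reach the record. Participants are treated as independent.

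Formula: P(no harm recorded) = (1 − p·s)^n.

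Example: p = 0.10, s = 0.5, n = 30 gives (1 − 0.05)^30 = 0.215.

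| n | p | s = 1 | s = 0.75 | s = 0.5 | s = 0.25 |
|---|---|---|---|---|---|
| 30 | 5% | 21.5% | 31.8% | 46.8% | 68.6% |
| 30 | 10% | 4.2% | 9.6% | 21.5% | 46.8% |
| 30 | 20% | 0.1% | 0.8% | 4.2% | 21.5% |
| 24 | 10% | 8.0% | 15.4% | 29.2% | 54.5% |

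Fixing the number harmed at 3 of 30 instead gives (1 − s)^3: 0.5^3 = 12.5% at s = 0.5, 0.7^3 = 34.3% at s = 0.3 and 0.8^3 = 51.2% at s = 0.2. The direction is the same.

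If no harm is recorded, the one-sided 95% upper limit on the recorded rate is 1 − 0.05^(1/n): 9.5% at n = 30 and 11.7% at n = 24. That much is due to sample size alone. The limit on the true rate is this figure divided by s. At s = 0.5 it becomes 0.095/0.5 = 19.0% at n = 30 and, from the unrounded limit, 23.5% at n = 24.

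**The case against.** A reader might infer that harms count only if volunteered, and that the report is bound to come out at none. The document does not support either. The reporting sentence covers any unintended harm and sets no rule of ascertainment. The condition that a participant reports distress stands in a separate sentence, about when support is offered. Nor is it true that nobody asks. Drop-outs are asked why they left, all participants are invited to focus groups, and the person collecting those data is from a different institution and was not known to participants beforehand. Those points stand, and they limit the conclusion to possible under-recording.

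It can also be said that a condensed article may leave harms forms and interview guides to the full protocol. That has force for such detail. It has less force here, because the article itself names the trigger, the responder and the recorder, itemises the surveys, lists the focus-group topics and prints a week-by-week schedule. What it describes is a passive method.

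Other objections stand in full. The probabilities above rest on assumed inputs. No passage makes an absence of harms a condition for proceeding to a larger study; the stated targets concern recruitment, completion and participation. A count of participants whose scores worsened, with no threshold and no control arm, in a workforce measured during the pandemic, would mix noise and workload with any effect of the course. For a study described as low-risk, recording by the investigators is a defensible choice if the sources that feed the record are stated.

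**Conclusion.** The concern holds in a limited form. The one stated route into the harms record is a participant's own report, the record is kept by the two people who deliver and facilitate the course, and the sources that do ask participants something are not joined to it. Harms may be under-recorded, and few or none recorded could not be read as reassurance.

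The direction is clear, but the size is not known. It depends on the share of harms captured, which the document does not allow one to estimate. Under the assumed 10% risk with 30 participants, the chance of an empty record runs from 4.2% at full capture to 46.8% at one-quarter capture. This does not undermine the feasibility outcomes. It affects one promised finding, and the change is worth making because it is cheap.

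**What to change.** - Add one neutral item on unwanted effects of the course to whichever of the t1 to t3 surveys are still open, and ask the same question at the drop-out contact.
- State that harms raised in drop-out reasons and in the focus groups, as collected by the qualitative researcher, are carried into the harms report.
- Report by source the number asked, the number answering and the number saying yes. For time-points already passed, describe any finding of no harms as limited by passive capture.
- If individual worsening from T0 to T3 on stress and wellbeing is shown, fix the threshold before analysis and present it descriptively, not as a count of course harms.
- Say how a harm disclosed under a Participant ID is handled. The Confidentiality paragraph says that the ID link is "only accessed if the participant has forgotten their ID and needs to be reminded", so as written a survey answer could not be followed up with the person. The two provisions must be reconciled.

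Cost: one item on a 90-item survey, one question at drop-out, one table and a minor amendment. The Study status section says that collection is under way and ends in December 2021, so early time-points may be lost. Carrying existing drop-out reasons and focus-group reports into the harms report needs no new data collection.
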